### Standard operation procedures for quality assurance

We have established detailed standard operating procedures for this clinical trial and have educated all practitioners and set qualification standards to make sure the patients are treated with high standards and in accordance with the trial protocol. Practitioners and medical equipment managers attended a 2-day training workshop about the trial procedures and were educated on methods for taking a picture of the patient’s face and how to examine the DITI, serum cortisol, DHEA-S, VAS, KAGS and IGA.

A written protocol and standardized recording documents will be provided. All practitioners and outcome assessors will be blinded to group allocations, and medical equipment managers will not participate in the interventions.

### Adverse events and safety monitoring

All unexpected adverse events related to CBT or the placebo intervention will be reported to the investigator by participants and written on the individual case report form by the investigator. Safety will be assessed by the reporting of clinical laboratory tests and adverse events. Clinical laboratory tests, including AST / ALT and creatinine, will be performed at screening and week 8 (the end of the trial). Each participant will be monitored for adverse events (pain at acne lesions or other sites, nausea/vomiting, fatigue, allergic reaction, and any adverse events related to intervention) after each visit.

### Statistical methods

#### Statistical analysis plan

Statistical analyses will be conducted on both intension-to-treat (ITT) and per-protocol (PP) bases, with a 95 % confidence interval using SPSS version 12.0 for Windows. Based on the ITT population, the primary outcome and safety outcome will be tested. Secondary outcome will be analyzed on both the ITT and PP populations. The ITT analysis will consider all randomized participants with at least one measurable outcome value during the study. Missing values from drop-out participants will be imputed by the last observation carried forward (LOCF) method. Data will be displayed as the mean ± standard deviation (SD) for continuous data or n (%) for categorical data.

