### Outcome measures

#### Primary outcome

Primary outcome will be presented as the mean percentage change of inflammatory lesion counts from baseline to the end of the trial [8, 9].

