### Withdrawal, dropout, discontinuation and compliance

Participants will be allowed to withdraw at any time during this clinical trial. Participants who wish to withdraw will be offered the option to cease trial intervention, but continue the visits for outcome measurement. Participants who withdraw will be followed to investigate the reason for withdrawal. Participants may be advised to discontinue this trial if there is a serious intervention-related adverse event or if the participant is noncompliant with the study procedure. CBT or placebo remaining after each session will be quantified in order to measure and enhance medication compliance. Participants whose compliance with CBT or placebo is ≤ 80 % of the total will be considered to have dropped out.

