### Baseline data and outcome data

An independent *T* test will be performed for comparison of the baseline values between the CBT and placebo groups. The independent *T* test will be used to examine the mean percentage change of the inflammatory/non-inflammatory lesion counts, the differences in the temperatures of the DITI points on the face, sebum level, serum cortisol, DHEA-S, VAS, and IGA at baseline and at the end of the trial (at week 8) between the CBT treatment and placebo control groups. Safety tests (AST, ALT and creatinine) will be analyzed using the independent *T* test at screening and at the end of the trial (at week 8) between the CBT treatment and placebo control groups. A repeated measured analysis of covariance (ANCOVA) test will be used to examine the percentage change of inflammatory and non-inflammatory lesions, differences in the temperatures of the DITI points on the face, VAS, and IGA at weeks 0, 4, and 8 when controlling for baseline and other covariates. The correlation between inflammatory lesion count and the facial skin superficial temperature points at baseline, 4 weeks, and 8 weeks will be examined using the Pearson correlation test. Additionally, we will analyze the correlation between the temperatures of the DITI points and the severity of the KAGS using the Pearson correlation test. The change of KAGS from baseline to week 8 will be assessed using a Chi-square test or Fisher’s exact test. All adverse events reported during the study will be included in the case report forms; the incidence of adverse events will be calculated. The percentage of subjects with adverse events in each group will be calculated and compared using a Chi-square test or Fisher’s exact test. The evaluation of blinding success between the actual treatment and the perceived treatment allocations will be performed using a Chi-square test or Fisher’s exact test.

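### LOCF is the only stated handling of missing week-8 counts in the primary analysis and can bias the arm difference; whether non-compliers' observed counts are kept is left open

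*Protocol article*

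**What the plan says.** All references are to the protocol article.

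- **Primary outcome.** "Primary outcome will be presented as the mean percentage change of inflammatory lesion counts from baseline to the end of the trial". Under Baseline data and outcome data, an independent t "test will be used to examine the mean percentage change of the inflammatory/non-inflammatory lesion counts".
- **Population.** Under Statistical analysis plan: "Based on the ITT population, the primary outcome and safety outcome will be tested". That set is described as follows: "The ITT analysis will consider all randomized participants with at least one measurable outcome value during the study". Whether a baseline value alone is enough is not said.
- **Missing data.** The same section continues: "Missing values from drop-out participants will be imputed by the last observation carried forward (LOCF) method". No other method and no sensitivity analysis is named.
- **Who is a dropout.** Under Withdrawal, dropout, discontinuation and compliance: "Participants whose compliance with CBT or placebo is ≤ 80 % of the total will be considered to have dropped out". The same paragraph says: "Participants who wish to withdraw will be offered the option to cease trial intervention, but continue the visits for outcome measurement".
- **Visits and planning figures.** Table 2 and Secondary outcomes place the counts used for follow-up at weeks 0, 4 and 8. Sample size assumes mean changes of -32.4% (SD 44) and -15.1% (SD 44.9), 28 participants per arm and 20% dropout.

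**The concern.** LOCF recovers a dropout's week-8 value only if the count stays where it was when last seen, or if the errors happen to cancel. The protocol's own planning figures expect both arms to change by week 8, and by different amounts. With one intermediate visit, the value carried forward is the week-4 count or, if a baseline value alone qualifies for ITT, a change of 0%. The t test then treats that value as a real week-8 observation.

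At the planned 20% dropout, about 11 of 56 participants (0.20 × 56 = 11.2) would have such a value. How far the estimate moves depends on when people leave and how evenly they leave across arms, and neither is known in advance. The results matter beyond this trial, because Sample size says that its mean and SD will be used to size larger ones.

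The compliance rule adds a second question. Adherence is measured after randomisation and treatment can affect it. If the dropout label decided whose week-8 count is used, the comparison would depend partly on adherence and would no longer be ITT. The text does not settle whether it does.

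**Working it through.** **Planning figures.** Difference: 32.4 − 15.1 = 17.3 points in favour of CBT. Pooled SD: √[(44² + 44.9²)/2] = 44.45. Effect size: 17.3/44.45 = 0.389, which agrees with the stated 0.39. The 28 per arm is taken as given here; whether it follows from that effect size is a separate question.

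**Assumptions not in the document.** Dropouts would have had the same week-8 mean as completers in their arm. The carried value has mean f × m, where m is the arm's week-8 mean. Take f = 0.5 for a week-4 count with half the effect reached, and f = 0 for baseline carried forward.

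**Formula.** With dropout proportion p, the arm mean under LOCF is m × [1 − p(1 − f)].

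| Dropout CBT / placebo | f | CBT mean | Placebo mean | Difference favouring CBT |
|---|---|---|---|---|
| 20% / 20% | 0.5 | -32.4 × 0.90 = -29.16 | -15.1 × 0.90 = -13.59 | 15.57 |
| 20% / 20% | 0 | -32.4 × 0.80 = -25.92 | -15.1 × 0.80 = -12.08 | 13.84 |
| 30% / 10% | 0.5 | -32.4 × 0.85 = -27.54 | -15.1 × 0.95 = -14.345 | 13.195 |
| 30% / 10% | 0 | -32.4 × 0.70 = -22.68 | -15.1 × 0.90 = -13.59 | 9.09 |
| 10% / 30% | 0.5 | -32.4 × 0.95 = -30.78 | -15.1 × 0.85 = -12.835 | 17.945 |
| 10% / 30% | 0 | -32.4 × 0.90 = -29.16 | -15.1 × 0.70 = -10.57 | 18.59 |

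**No true effect.** Set both arms to -30% with 10% dropout on CBT and 30% on placebo. For f = 0.5 the arm means are -28.5 and -25.5, a spurious 3.0 points for CBT. For f = 0 they are -27.0 and -21.0, a spurious 6.0.

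**Standard error.** With complete data it is 44.45 × √(2/28) = 11.9. With only the observed week-8 values at 20% dropout (28 × 0.8 = 22.4 per arm) it is 44.45 × √(2/22.4) = 13.3. A simulation used 28 per arm, 20,000 runs per scenario, dropout at random, week-4 SD 22 or 44 and a week-4 to week-8 correlation of 0.6 (the last three also assumed):

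- At 20% dropout in each arm with the planned effect, the LOCF standard error was 10.9 to 11.9, which is 10% to 18% below 13.3. The upper end, with week-4 SD 44, is about the complete-data value.
- In every scenario it agreed closely with the actual spread of the LOCF estimate.
- With no effect, type I error stayed near 5% under equal dropout and was about 5% to 9% under a 30%/10% split in either direction.
- With the planned effect, coverage of the true difference was 94% to 95% under equal dropout and fell to 88% in the worst case (30% on CBT, 10% on placebo, baseline carried).

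**The compliance rule beside the imputation rule.** One section calls a participant with compliance of 80% or less a dropout. The other imputes missing values of dropouts. A week-8 count that was taken is not missing, so read literally it would be used. But no sentence says that it is kept, and none says that it is set aside.

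**The case against.** Three stronger readings are tempting, and the document supports none of them.

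1. **That observed week-8 counts of non-compliers are overwritten.** Only missing values are imputed, and the ITT description removes nobody for poor compliance. The dropout label may serve the per-protocol set or the dropout tally. Nor is it certain that such counts will exist, since withdrawers are only offered the option to "but continue the visits for outcome measurement". What stands is an ambiguity to be resolved.
2. **That the primary estimate is biased.** It can be. Equal dropout at the planned rate shrinks the effect, which is conservative, and does not raise the false-positive rate. The case that favours CBT when the effect is real adds only 0.6 to 1.3 points, against a complete-data standard error of 11.9. Nothing in the document suggests a 10%/30% split, and the 6-point figure also needs every dropout to leave before week 4.
3. **That the confidence interval is too narrow.** The LOCF standard error is smaller than that of an analysis reflecting the lost information, but it describes the LOCF estimate's own variability correctly, and in some scenarios it is no smaller than with complete data.

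The benchmark is also open to challenge. Letting dropouts resemble completers means that people who stop treatment still reach the full -32.4%. If they lose benefit, the true treatment-regardless difference is below 17.3, and the shortfalls above are overstated.

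Finally, a repeated-measures ANCOVA over weeks 0, 4 and 8 with baseline adjustment is already planned. It is not named as the primary test, however, and is not said to run on observed data without LOCF. It therefore does not remove the point.

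**Conclusion.** The point holds in limited form. LOCF is the sole stated method for missing values in the ITT primary analysis, and it is a weak choice for a count expected to keep changing between visits. Under the two assumptions above, equal 20% dropout costs 10% to 20% of a 17.3-point effect. Unequal dropout can move the estimate to anywhere between 9.1 and 18.6, or create 3 to 6 points where there is no effect. Size and direction depend on the timing and balance of dropout, so these figures show a range and do not predict the result. Understated uncertainty is possible relative to an analysis that reflects the lost information, but not in every scenario.

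That LOCF is fixed for the primary analysis is plain from the text. How observed counts of participants with compliance of 80% or less will be treated is not, and the two sections need to be reconciled before unblinding.

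**What to change.** 1. Make the primary analysis a mixed model for repeated measures on the observed percentage changes at weeks 4 and 8. Include arm, visit, arm-by-visit interaction, baseline count and the stratification factor used at randomisation (the article says randomisation is stratified but does not name the factor). Report the week-8 contrast between arms. Keep LOCF as a sensitivity analysis.
2. Add a sentence that reconciles the withdrawal and analysis sections: every observed outcome enters the ITT analysis whatever the compliance, and the 80% threshold defines the per-protocol set only.

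The cost is a change of wording and a mixed-model procedure, using data already scheduled for collection. The small downside is that the model assumes data are missing at random. That cannot be verified, but it is weaker than assuming that counts stop changing once a participant leaves.

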### Baseline data and outcome data

An independent *T* test will be performed for comparison of the baseline values between the CBT and placebo groups. The independent *T* test will be used to examine the mean percentage change of the inflammatory/non-inflammatory lesion counts, the differences in the temperatures of the DITI points on the face, sebum level, serum cortisol, DHEA-S, VAS, and IGA at baseline and at the end of the trial (at week 8) between the CBT treatment and placebo control groups. Safety tests (AST, ALT and creatinine) will be analyzed using the independent *T* test at screening and at the end of the trial (at week 8) between the CBT treatment and placebo control groups. A repeated measured analysis of covariance (ANCOVA) test will be used to examine the percentage change of inflammatory and non-inflammatory lesions, differences in the temperatures of the DITI points on the face, VAS, and IGA at weeks 0, 4, and 8 when controlling for baseline and other covariates. The correlation between inflammatory lesion count and the facial skin superficial temperature points at baseline, 4 weeks, and 8 weeks will be examined using the Pearson correlation test. Additionally, we will analyze the correlation between the temperatures of the DITI points and the severity of the KAGS using the Pearson correlation test. The change of KAGS from baseline to week 8 will be assessed using a Chi-square test or Fisher’s exact test. All adverse events reported during the study will be included in the case report forms; the incidence of adverse events will be calculated. The percentage of subjects with adverse events in each group will be calculated and compared using a Chi-square test or Fisher’s exact test. The evaluation of blinding success between the actual treatment and the perceived treatment allocations will be performed using a Chi-square test or Fisher’s exact test.

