### Randomization and allocation concealment

Using a stratified block randomization method, 56 eligible patients will be randomly allocated to the CBT or placebo groups in a 1:1 ratio in blocks of 4. Random numbers will be generated by a computerized random-number generator using the block-randomization method of a software program (R 3.2.2) for sequence generation by an independent statistician. The randomization lists will be concealed in a lightproof sealed envelope. The sealed envelopes will be kept by the independent statistician of the study. Participants, investigators and outcome assessors will be blinded to the treatment allocation throughout the course of the study.

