### Sample size

Calculation of the sample size for this trial was based on the effect size of the primary outcome, mean percent change of inflammatory acne lesion counts from baseline to week 8, reported in a previously published study [11]. The mean and standard deviation (SD) of the mean percent change of inflammatory acne lesion counts were -32.4 ± 44 and -15.1 ± 44.9 for the active treatment and control groups, respectively. To achieve 80 % power (β = 0.20), a significance level of 0.05 (α) in a two-tailed test, calculated using Cohen's d effect size values for t-tests (0.39), 28 participants, based on an estimated 20 % dropout rate, are needed for each group. This results in a required total of 56 for the trial. The mean and SD of the mean percent change of inflammatory acne lesion counts from this pilot study will be used for recalculation of the sample size for larger trials.

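### The primary outcome has two analyses and neither is named primary; the apparent one, an unadjusted t test, is valid but leaves the baseline count and the randomisation strata unused

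*Protocol article*

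**What the plan says.** - **Primary outcome** (Primary outcome): "Primary outcome will be presented as the mean percentage change of inflammatory lesion counts from baseline to the end of the trial".
- **First analysis** (Baseline data and outcome data): an independent t test, with no covariate, "will be used to examine the mean percentage change of the inflammatory/non-inflammatory lesion counts" between the arms at week 8.
- **Second analysis** (same section): "A repeated measured analysis of covariance (ANCOVA) test will be used to examine the percentage change of inflammatory and non-inflammatory lesions", with other outcomes, "at weeks 0, 4, and 8 when controlling for baseline and other covariates". The other covariates are not listed.
- **Randomisation** (Randomization and allocation concealment): "Using a stratified block randomization method, 56 eligible patients will be randomly allocated to the CBT or placebo groups". Allocation is equal and the block size is four. No stratification factor is named.
- **Planning basis** (Sample size): "To achieve 80 % power (β = 0.20), a significance level of 0.05 (α) in a two-tailed test", with Cohen's d for t tests of 0.39 and 28 participants per group.

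No sentence says which of the two analyses decides the trial. The sample size calculation makes the t test the apparent choice.

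**The concern.** Two analyses of the primary variable, one unadjusted and one adjusted, can give different p-values. Without a stated order, a reader of the results cannot tell which was meant to be decisive.

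The apparent choice also sets aside information that the trial already holds.

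- **Baseline count.** Dividing by baseline does not make percent change independent of baseline. Entry requires more than 10 inflammatory lesions, and selection on a threshold produces regression to the mean, so patients with high counts tend to show larger relative falls in either arm. With 28 per arm, the standard error of a standardised baseline difference is √(2/28) = 0.27 SD, so chance imbalance is common.
- **Strata.** Stratified blocks balance the arms on the strata, which lowers the true variance of the treatment difference if the strata are prognostic. A t test without the strata does not credit that reduction, so its standard error is then too large.

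What is at stake is precision, in a trial that has little of it.

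**Working it through.** **1. The plan's own figure.** Inputs from Sample size: mean changes −32.4 (SD 44) and −15.1 (SD 44.9).

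- Difference = 32.4 − 15.1 = 17.3. Pooled SD = √((44² + 44.9²)/2) = 44.45. d = 17.3/44.45 = 0.389, which matches the stated 0.39.
- n per arm = 2(1.96 + 0.84)²/0.389² ≈ 104. With 20% dropout, 104/0.8 = 130 per arm, or 260 in total. The stated 28 per arm (56 in total) is not reproduced.
- Power of the t test at d = 0.39, two-sided 5%: 30% with 28 per arm, and 24% with 22 per arm (28 × 0.8 = 22.4 after dropout).

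The sample size is a separate matter. It is used here only as the starting point for power.

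**2. Gain from adjusting for baseline.** The article gives no correlation, so each of these rests on an assumption.

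*(a) Log-scale change score.* With equal variances and baseline to week-8 correlation r, ANCOVA variance / change-score variance = (1 − r²)/(2(1 − r)) = (1 + r)/2. Power uses d/√ratio.

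| r (assumed) | variance ratio | reduction | power, 28 per arm | power, 22 per arm |
|---|---|---|---|---|
| 0.3 | 0.65 | 35% | 43% | 35% |
| 0.5 | 0.75 | 25% | 38% | 31% |
| 0.7 | 0.85 | 15% | 34% | 28% |

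This is an optimistic guide, because the trial's outcome is raw percent change.

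*(b) Raw percent change.* Simulated with assumed lognormal counts (log SD 0.6) and entry above 10 lesions, adjustment for baseline removes about 7% of the variance at r = 0.7 and 14% at r = 0.3. That corresponds to a correlation between baseline and percent change of √0.07 = 0.26 to √0.14 = 0.37 in absolute value. A narrower spread of counts moves the figure up towards (a). If relative change is unrelated to baseline, the gain is zero. At a 14% reduction, d/√0.86 = 0.42 and power with 28 per arm is about 34%.

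*(c) By correlation ρ between covariate and outcome.* Residual SD = 44.45 × √(1 − ρ²). Power with 28 per arm is 30%, 32%, 38% and 52% at ρ = 0, 0.3, 0.5 and 0.7. For 80% power the residual SD must fall to 17.3/((1.96 + 0.84)√(2/28)) ≈ 23.1, so ρ = √(1 − (23.1/44.45)²) ≈ 0.85.

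**3. Effect of leaving out the strata.** Simulation of 20,000 trials per scenario: N = 56, blocks of 4, two equal strata (assumed, since none are named). R² is the share of outcome variance explained by the strata.

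| strata R² (assumed) | type I error, t test | power, t test | power, stratum-adjusted |
|---|---|---|---|
| 0 | 4.9% | 30% | 30% |
| 0.10 | 3.8% | 28% | 32% |
| 0.25 | 2.4% | 26% | 38% |

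At R² = 0.25 the t test's average estimated standard error is 0.267 SD against a true 0.231 SD. At R² = 0 there is no discrepancy.

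**The case against.** The strongest reply is that baseline adjustment is already planned. The repeated-measures ANCOVA covers the primary variable, includes week 8 and controls for baseline. That stands: a reader might infer from the t test that the plan ignores baseline, and it does not. But the ANCOVA is not designated primary, the trial is not sized on it, and it runs over weeks 0, 4 and 8, where percent change at week 0 is zero by construction. It leaves open which result counts.

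Secondly, the strata may be among the unnamed covariates. That also stands. The article does not support a claim that no analysis includes them; it shows only that the t test does not. Listing the factors is something an article may leave to a fuller document.

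Thirdly, a reader might infer that an unadjusted t test after stratified randomisation is invalid, with a wrong standard error and false positives. The calculations contradict this. Any error is conservative, it appears only if the strata are prognostic, and its size cannot be worked out without knowing the strata.

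Finally, percent change already uses baseline as its denominator, so further adjustment may gain little, and the article calls the trial a pilot. Both are fair, and both limit the size of the point. Neither is a reason to leave the primary analysis undesignated.

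**Conclusion.** The point holds as one of efficiency and designation. The apparent primary analysis is a valid but inefficient t test, beside an adjusted analysis of the same variable with no stated precedence.

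The gain rests on assumed correlations: roughly 0 to 15% less variance on the percent-change scale (lognormal counts), and 15 to 35% for a log-scale change score with r from 0.7 down to 0.3. In power at d = 0.39 with 28 per arm, that is 30% rising to about 34%, or to 43% at the optimistic end. The stratum effect ranges from nothing to the figures simulated above, which assume two equal strata.

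It would be tempting to present adjustment as the answer to low power. It is not: a baseline correlation of about 0.85 would be needed for 80%. The change is worth making because it is nearly free and settles which result is decisive.

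**What to change.** State one primary analysis: ANCOVA of week-8 percent change in inflammatory lesions on arm, with baseline inflammatory count and the stratification factors actually used in randomisation as covariates, two-sided 5%, reporting the adjusted difference with its 95% confidence interval. Name those factors. Keep the independent t test and the repeated-measures ANCOVA as supporting analyses, and list the latter's other covariates.

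The cost is a sentence or two in the analysis section and a few degrees of freedom, depending on the number of strata. No new data are needed: Table 2 has lesions counted at baseline, and the strata must be known in order to randomise.

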**Methods/design:**

A randomized, double-blind, parallel-group, and placebo-controlled trial will be conducted. Fifty-six participants with acne vulgaris will be randomized into one of two groups: the CBT or placebo groups. After randomization, participants will be prescribed either CBT or placebo three times a day at a dose of 5 g after meals for 8 weeks. The following outcome measurements will be used in the examination of subjects: the mean percentage change and the count change of the inflammatory and non-inflammatory acne lesions, the temperature of facial points on digital infrared thermal imaging (DITI), serum cortisol, serum dehydroepiandrosterone-sulfate (DHEA-S), visual analogue scale (VAS), investigator global assessment (IGA), and severity score on the Korean Acne Grading System (KAGS) from baseline to the end of the trial.

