### Secondary outcomes

Secondary outcomes will evaluate the mean percentage change of non-inflammatory lesions and the total of both inflammatory and non-inflammatory lesions, the differences in temperatures of the DITI points on the face, Visual Analogue Scale (VAS) [score 0 (no symptoms) to 100 (severe symptoms)], and the Investigator Global Assessment scale for Facial Acne Vulgaris (IGA; after evaluation from score 0 (clear) to 4 (severe)) [10] from baseline to the end of the trial (at 8 weeks) between CBT treatment and the placebo control groups. Serum cortisol and dehydroepiandrosterone-sulfate (DHEA-S) will be assessed using clinical laboratory tests at weeks 0 (baseline) and 8 (end of the trial).

VAS and IGA will be checked every session from baseline (just before randomization) through the 8 weeks after randomization. A Lumix DMC-LX2 digital camera (Panasonic, Osaka, Japan) will be used to photograph the front and both sides of each patients face, so that the inflammatory and non-inflammatory lesions can be counted independently at weeks 0 (baseline), 4 and 8 (end of the trial) by a clinical specialist who has been in clinical practice for more 5 years. We will consider black and white head comedones to be non-inflammatory lesions and the inflammatory papules, pustules and cysts to be inflammatory lesions.

Correlations between the inflammatory lesion count and the temperatures of the DITI points at baseline, 4 weeks, and 8 weeks, and the frequency of abnormal liver and kidney function during this trial will also be secondary outcomes. Additionally, we will analyze the correlation between the temperatures of the DITI points and the severity of the Korean Acne Grading System (KAGS) at baseline and the end of the trial (at 8 weeks). Finally, we will analyze the success rate of blinding between the actual treatment and the perceived treatment allocations.

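### Serum cortisol and DHEA-S are compared only by an unadjusted t test, and VAS and IGA by two analyses with no stated lead, although pre-treatment values are collected for all four

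*Protocol article*

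**What the plan says.** Under Secondary outcomes, VAS and IGA are to be evaluated "from baseline to the end of the trial (at 8 weeks) between CBT treatment and the placebo control groups". For cortisol and DHEA-S the same section says only that they "will be assessed using clinical laboratory tests at weeks 0 (baseline) and 8 (end of the trial". The abstract lists all four among its outcome measurements and closes that list with "severity score on the Korean Acne Grading System (KAGS) from baseline to the end of the trial".

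Under Baseline data and outcome data, the t-test sentence covers the lesion percentage changes and then "the differences in the temperatures of the DITI points on the face, sebum level, serum cortisol, DHEA-S, VAS, and IGA at baseline" and at week 8. The part of it that sets the time points for the four outcomes reads "serum cortisol, DHEA-S, VAS, and IGA at baseline and at the end of the trial (at week 8". A later sentence adds a second method: "A repeated measured analysis of covariance (ANCOVA) test will be used to examine the percentage change of inflammatory and non-inflammatory lesions". Its list of variables ends with "VAS, and IGA at weeks 0, 4, and 8 when controlling for baseline and other covariates". VAS and IGA are in that model; cortisol and DHEA-S are not.

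Table 2 schedules VAS and IGA at baseline, week 4 and week 8, and the blood tests at screening and week 8. Every one of the four outcomes therefore has a value from before treatment.

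**The concern.** There are two loose ends.

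- For the hormones, the article commits to a between-group test that leaves the pre-treatment value out as a covariate. In a trial of 56 people the arms can differ noticeably at baseline by chance, and an unadjusted test lets part of that difference into the result.
- For VAS and IGA, two analyses are planned that can give different answers on the same data: one adjusted for baseline and one not. The article does not rank them. The t test's time wording also does not match the outcome section, which frames VAS and IGA as running from baseline to the end of the trial.

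What is at stake is precision and clarity in four secondary outcomes, and for VAS and IGA the freedom to choose between results afterwards.

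**Working it through.** The plan states no figure on this point, so there is none to reproduce. The check has two parts.

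**Which quantity does the t test compare?** The text supports two readings.

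- *Levels at each time.* The article names two time points rather than an interval. The next sentence treats AST, ALT and creatinine in the same way, with no mention of a difference. Where change is meant for KAGS, the section says so.
- *Differences between the two times.* The reference to differences that opens the list may govern every item in it. The same time phrase also attaches to lesion percentage change, which cannot be a level at baseline. And the sentence before already plans a baseline t test, so a second one would be redundant.

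Neither reading can be excluded, so both are carried through.

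**What does each reading cost?** Inputs:

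- n = 28 per arm (Sample size: "28 participants, based on an estimated 20 % dropout rate, are needed for each group").
- The correlation rho between the pre-treatment and week-8 values is not given for any of these outcomes. I assume 0.2, 0.5 and 0.8.
- Equal SDs at both times and in both arms (assumption). Results are in units of that SD.

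Standard error (SE) of the difference between arms:

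- Level test at week 8: sqrt(2/28) = 0.267. This is also the SE of a chance baseline difference.
- Unadjusted change: 0.267 × sqrt(2(1 − rho)).
- Baseline-adjusted: 0.267 × sqrt(1 − rho²).

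If the arms happen to differ at baseline by one such SE (0.267 SD), the expected shift is rho × 0.267 in the level test and −(1 − rho) × 0.267 in the change test. Baseline adjustment removes it.

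| | rho 0.2 | rho 0.5 | rho 0.8 |
|---|---|---|---|
| SE, level | 0.267 | 0.267 | 0.267 |
| SE, unadjusted change | 0.338 | 0.267 | 0.169 |
| SE, baseline-adjusted | 0.262 | 0.231 | 0.160 |
| Adjusted ÷ level | 0.98 | 0.87 | 0.60 |
| Change ÷ level | 1.26 | 1.00 | 0.63 |
| Shift, level test | +0.05 | +0.13 | +0.21 |
| Shift, change test | −0.21 | −0.13 | −0.05 |

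The adjusted comparison has the smallest SE in each column. Moving from levels to an unadjusted change score would not be a cure: it admits imbalance with the opposite sign and is less precise than the level test when rho is below 0.5. The formulas ignore the small cost of estimating the covariate's slope, so at low rho the gain over the level test is close to nil.

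**The case against.** The strongest reply is that this is a loosely worded sentence about secondary outcomes in a trial whose Sample size section calls it a pilot study. VAS and IGA already have a baseline-controlled model, and which of two listed analyses leads is often left to an analysis plan that is not shown here. Much of this stands. It limits the VAS and IGA part to a clarification. It does not reach cortisol and DHEA-S, for which the article names one between-group test, and that test is unadjusted.

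A reader might go further and infer four things that the documents do not support.

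- *That raw levels are definitely tested.* The sentence can equally be read as testing differences.
- *That the hormones are defined as change and the analysis contradicts this.* The outcome section says only that they are assessed at weeks 0 and 8, which agrees with the t-test wording. Only the abstract's closing phrase points to change, and it may simply give the measurement period.
- *That a different effect is being estimated, or that the result is biased.* Under randomization the expected baseline difference is zero. The week-8 level difference and the difference in mean change therefore estimate the same effect, and both are unbiased.
- *That baseline imbalance is left uncontrolled for VAS and IGA.* The planned ANCOVA addresses it.

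**Conclusion.** The point holds in a limited form. Cortisol and DHEA-S have only an unadjusted t test, with wording that leaves open whether levels or differences are compared. VAS and IGA have that test alongside a baseline-controlled ANCOVA, with no lead stated.

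The loss is precision and protection against the particular imbalance that occurs, not bias. Adjustment lowers the SE relative to a level test by 2%, 13% and 40% at rho 0.2, 0.5 and 0.8. Relative to an unadjusted change test the reduction is largest at low rho (0.262 against 0.338 at rho 0.2) and small at high rho (0.160 against 0.169 at rho 0.8).

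These figures rest on assumed correlations, equal SDs and 28 analysed per arm. They are only a rough guide for IGA, which is scored 0 to 4. I give no power figures: the planning effect of 0.39 belongs to percentage change in inflammatory lesions and says nothing about these four outcomes. The primary outcome is not affected by this point.

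**What to change.** In Baseline data and outcome data:

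- **Cortisol and DHEA-S:** replace the t test with a comparison of arms on the week-8 value, with the pre-treatment value as covariate. Report one estimate and 95% confidence interval per hormone. Using change as the response with the same covariate gives the same treatment estimate, so this settles the level-or-change question. State that the covariate is the single pre-treatment sample, which Table 2 places at screening and Secondary outcomes calls week 0.
- **VAS and IGA:** name the week-8 contrast between arms from the planned baseline-adjusted ANCOVA as the deciding analysis, and drop the t test as an outcome analysis.
- **Baseline values:** report them descriptively, as mean and SD by arm.

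The cost is wording and one degree of freedom per model. No extra participants, visits or measurements are needed.
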